## Abstract

**Background:**

Dystonic cerebral palsy is primarily caused by damage to the basal ganglia and central cortex. The daily care of these patients can be difficult due to dystonic movements. Intrathecal baclofen treatment is a potential treatment option for dystonia and has become common practice. Despite this widespread adoption, high quality evidence on the effects of intrathecal baclofen treatment on daily activities is lacking and prospective data are needed to judge the usefulness and indications for dystonic cerebral palsy. The primary aim of this study is to provide level one clinical evidence for the effects of intrathecal baclofen treatment on the level of activities and participation in dystonic cerebral palsy patients. Furthermore, we hope to identify clinical characteristics that will predict a beneficial effect of intrathecal baclofen in an individual patient.

**Methods/Design:**

A double blind placebo-controlled multi-center randomized clinical trial will be performed in 30 children with dystonic cerebral palsy. Patients aged between 4 and 25 years old with a confirmed diagnosis of dystonic cerebral palsy, Gross Motor Functioning Classification System level IV or V, with lesions in the cerebral white matter, basal ganglia or central cortex and who are eligible for intrathecal baclofen treatment will be included. Group A will receive three months of continuous intrathecal baclofen treatment and group B will receive three months of placebo treatment, both via an implanted pump. After this three month period, all patients will receive intrathecal baclofen treatment, with a follow-up after nine months. The primary outcome measurement will be the effect on activities of and participation in daily life measured by Goal Attainment Scaling. Secondary outcome measurements on the level of body functions include dystonia, spasticity, pain, comfort and sleep-related breathing disorders. Side effects will be monitored and we will study whether patient characteristics influence outcome.

**Discussion:**

The results of this study will provide data for evidence-based use of intrathecal baclofen in dystonic cerebral palsy.

**Trial registration:**

Nederlands Trial Register,
NTR3642

## Background

### Dystonic cerebral palsy

Cerebral palsy (CP) is a group of disorders caused by non-progressive disturbances that occurred in the developing fetal or early infant brain. The classification of cerebral palsy includes the classical neurological terms for central motor disorders: spasticity, dyskinesia and ataxia
[1,2]. Dyskinesia can be further differentiated into dystonia and choreoathetosis
[2]. Dystonia is described as an abnormal pattern of posture and/or movement that is involuntary, uncontrolled, recurring and occasionally stereotyped. These movements can interfere with daily care and may be painful and uncomfortable. The dyskinetic form of cerebral palsy, including the dystonic form, is in most patients caused by lesions in the basal ganglia. Additional lesions of the central cortex are found in some cases. This type of brain damage is a common pattern in asphyxiated infants born at term
[3].

### Treatment

The results of pharmacological treatment of severe dystonic CP have been rather disappointing. Positive effects on dystonia with levodopa, anticholinergic drugs or muscle relaxants including benzodiazepines and baclofen, have been reported by some authors
[4,5]. In addition, Albright and co-workers described an anti-dystonic effect of intrathecal baclofen (ITB) treatment. Despite the fact that studies on the effects of ITB on dystonic cerebral palsy are limited in number and the level of evidence is low, ITB is now common practice in the treatment of severe dystonic CP.

Not all patients are eligible for ITB treatment. The following criteria apply: 1. The etiology is preferably known; 2. Management of aggravating factors, such as pain and discomfort, should be optimal; 3. Other treatment options should have been explored. Oral pharmacological treatment with levodopa, anticholinergic drugs or muscle relaxants including benzodiazepines and baclofen must have been attempted and must have resulted in high oral dosages with either unacceptable side effects or insufficient efficacy; 4. The movement disorder should be so severe that it interferes with activities of daily life or quality of life; 5. Treatment goals should be clear and applicable and, to avoid disappointment, it is important that patients and parents understand these goals; 6. Patients and parents should be motivated and able to adhere to the requirements of treatment, such as the frequent pump fillings and checkups in the outpatient clinic; 7. Patients should have sufficient body size to allow pump implantation
[6].

### Objectives

The primary objective of the present study is to show whether ITB treatment improves activities of and participation in daily life (for example dressing, transfer, sitting in a wheelchair, hygienic care, speech) in dystonic CP patients. Certain patient characteristics, such as the location and severity of MRI lesions and Gross Motor Functioning Classification Score (GMFCS) level, might influence the effects of ITB treatment in patients with dystonic CP. Therefore, we will study whether individual patient characteristics (GMFCS, gender, age, MRI findings and co-medication) influence outcome and could be used in determining the indication for ITB in future patients. A secondary objective is to provide evidence for the effect of ITB on the level of body functions. The relevant clinical questions to be addressed are: 1. Does ITB decrease dystonia? 2. Does ITB decrease spasticity in dystonic patients? 3. Does ITB decrease pain? 4. Does ITB increase comfort? 5. Does ITB influence screening results of sleep-related breathing disorders? 6. What are the side effects of ITB?

## Methods/Design

### Study design

The design of the study is a double blind placebo-controlled multi-center randomized clinical trial. It will be conducted in the VU University Medical Center (VUMC) in Amsterdam and the Maastricht University Medical Center (MUMC) in Maastricht (both in the Netherlands). The Medical Ethical Committee of the VU University Medical Center approved the study. In both centers local practicability was granted subsequently. Subjects will be included over a period of two and a half years and they will participate in the study for one year. Figure 
1 shows the flow scheme for subjects and timing of measurements throughout the study.

**Figure 1 F1:**
[figure not shown]
Flow chart subjects.

### Participants

Thirty subjects will be recruited from the outpatient clinics of the pediatric neurology and pediatric rehabilitation departments of the VUMC and the MUMC. Table 
1 shows the inclusion and exclusion criteria. We selected ages between 4 and 25 years old because older patients often show secondary complications, such as contractures, that could introduce greater variation into both the effects of treatment and treatment goals. Furthermore, to achieve a homogeneous patient group, only GMFCS IV and V (non-walkers) will be included. All patients and/or their caregivers will sign an informed consent form before participating in the study.

**Table 1 T1:** Summary of inclusion and exclusion criteria

**Inclusion criteria**	**Exclusion criteria**
• Dystonic cerebral palsy	• Contra-indications for general anesthesia
• GMFCS IV or V	• Contra-indications for baclofen
• Eligible for ITB treatment using criteria of common practice	• Oral pharmacological treatment is sufficient
• Lesions on MRI (cerebral white matter, basal ganglia, central cortex)	• Inadequate knowledge of Dutch language
• Aged 4 to 25 years old	• Deep brain stimulation
• Able and willing to complete study protocol	• Ventriculoperitoneal drain
• Consensus about inclusion	• Other disorders interfering with treatment

### Sample size calculation

We will use goal attainment scaling (GAS) as our primary outcome measure. The within group change for the placebo group is anticipated to be 0, with a standard deviation (SD) of 8.5. For the intrathecal baclofen group, the within group change is anticipated to be 12.5, with a SD of 10. To achieve a power of 90% when testing for a difference in means using a two-tailed independent samples t-test and a significance level of 5%, a total of 13 subjects per group will be needed.

In a previous study in the VU University Medical Center, 4 infections occurred in 34 pump implantations
[7]. Ward and coworkers reported pump removal in 5.9% of the cases with infections following implantation
[8]. Extrapolating these numbers, inclusion of 30 patients is expected to lead to 3.5 infections and 1.2 pump removals. To prevent the study from becoming underpowered, due to unexpected protocol violations or subject dropout due to complications other than those related to intrathecal baclofen treatment, we will include 15 subjects per group.

### Intervention

Included subjects will be randomized in two groups. Group 1 will receive placebo treatment via an implanted micro-infusion pump for three months. Group 2 will receive ITB treatment via an implanted micro-infusion pump for three months. In our opinion, it is unethical to continue placebo treatment for more than three months. If interim analysis shows that subjects in one of the groups have significant disadvantages compared to the other group, the study will be prematurely terminated. On the other hand, we know from experience that dosages for some patients are still being modified three months after starting treatment. As a consequence, the effect of treatment in these patients may not yet be optimal, which may then result in no detectable effect of ITB treatment at that point. We will try to reduce this possible effect through frequent dose modification. Patients will be seen once or twice weekly to increase their dosage, until either a stable dosage or a maximal dosage of 800 μg/day is achieved.

Subjects will be assessed at three months and the effect of treatment in the two groups compared. Since determining the most beneficial pump setting can take more than three months and because the initial effect may recede in some cases, all subjects will receive subsequent ITB treatment for nine months. Following this 9 month period, clinical evaluation will be performed in order to determine long-term effects (see Figure 
1. Flow Chart of Subjects).

### Dosage

Patients with dystonia seem to require larger ITB doses than the doses used to treat spasticity
[9]. Albright and colleagues noticed a change in dystonia only after 4 days of continuous infusion
[10]. The effective dose of ITB was in the range of 350 to 750 μg/day
[9-11]. Since a screening period will not be included, we do not know how subjects will respond and which dose will be sufficiently effective. Therefore, the starting dosage will be 50 μg/24 h.

Dosage can be increased by 10-20% daily. When subjects are discharged from the hospital following pump implantation, they will be seen once a week or once every two weeks for dosage modification. After three weeks of increasing dosage, with disappearance of the effect of the increase, daily boluses will be administered to a maximum of four times a day, with a minimal interval of four hours. For the blinded part of the study, a maximum dosage of 800 μg/day will be administered. This is a reasonable estimation of the maximal dosage after three months. Since treatment during the study is blinded, the physician in charge of regular follow-up after pump implantation, including pump filling and dosage adjustments, will be unaware of the subject’s allocated group. To provide optimal treatment, pump settings will be individually altered to the extent that the physician would consider necessary, based on the findings of physical examination and parental and patient interview, as were the patient not participating in the study. As a consequence, the pump settings of subjects in the placebo group will be altered as if the patient was receiving ITB treatment.

Lack of response to ITB can be caused by pump or catheter dysfunction. Placebo treatment may also cause lack of effect and for this reason no action will be taken during the first three months of the study in cases where pump or catheter dysfunction would normally be suspected. An exception will be made when the condition of the patient requires otherwise, such as in the case of signs of withdrawal. One week after pump implantation, all patients will undergo X-ray of the spine to determine the position of the catheter tip. The catheter should be placed approximately at the fourth cervical level, and at least above the level of Th1.

### Outcome measures

Outcome measurements are defined on the levels of the International Classification of Functioning, Disability and Health (ICF) model of the World Health Organization (WHO). We distinguish the level of activities and participation and the level of body functions. Body functions are the physiological and psychological functions of body systems. Activities are defined as the execution of a task or action by an individual. Participation is involvement in a life situation
[12].

### Primary outcome measure

The primary outcome measurement will be on the level of activities and participation. Goal attainment scaling (GAS) will be used to measure the effect of ITB treatment. Using GAS, achievement of individual set goals can be quantified. This method was introduced for assessing outcomes in mental health settings and has been used in many other areas
[13,14]. Each subject has their own outcome measure, but statistical analysis is possible because they are scored in a standardized way. This procedure is time-consuming and requires about 45 minutes per child
[15,16]. However, after the scale is constructed, it should be possible to score a patient within 10 minutes
[17].

The procedure includes the following aspects:

1) Identification of goals:

Three main problems of daily care and function will be determined by caregivers. Goals will be set for these problems with the help of the team to ensure that goals are achievable. Goals should be specific, measurable, attainable, realistic and timely (SMART)
[13,14]. The target activity, specific support and time period should be specified and performance should be quantified using distance, frequency or time taken to accomplish a task
[14].

2) Weighing of goals:

Some goals will be more important for subjects than others
[13]. Goals can be assigned a weighing score by caregivers and a difficulty score by the team
[14]. We chose not to assign weighing scores since the weighted and unweighted scores are closely correlated
[18]. A value of 1 is applied to ‘weight’ in the formula described below.

3) Definition of expected outcomes:

Several approaches are described in literature, varying from 5 to 7 point scales
[14,15]. We will use a 6 point scale ranging from -3 to +2, since we wish to include both the possibility of partially achieving the set goal and to avoid a bottoming effect. Baseline scores will be allocated as -2. If the subject achieves the expected level, this is scored as 0. If a subject does not achieve the expected level but shows improvement, this is scored as -1. If they achieve more than the expected outcome, this is scored as +1 for somewhat more and +2 for much more. We chose to add a score of -3 in case of deterioration. Each goal level will be defined by the investigator so as to be as objective and observable as possible
[13].

4) Scoring goal attainment:

For each assessment, one assessor will make a standardized video recording during trials for each of the three functional ability goals. The recording procedure will be identical for all measurements. Another assessor, blinded for group allocation, will rate the subject’s performance from the video recordings. Although the GAS only simulates the subject’s own functional setting, parents were convinced that the outcome of scaling was representative of their own setting
[19].

Goal attainment scores will be recorded at baseline, after three months of blinded treatment and after nine months of ITB treatment. Goal attainment change scores will be determined by subtracting the baseline score from the outcome score. Subjects who achieve a GAS T-score >50 achieved their goals
[8]. Clinical relevance will be defined as an improvement of at least two points in at least one of the three goals
[19].

A single aggregated score (T-score) can be produced by a standardized mathematical formula: Overall GAS = 50+ 10∑(w_i_x_i_) / √((1-ρ) ∑w_i_^2^ + ρ(∑w_i_)^2^); W_i_ is the weight assigned to the goal, x_i_ is the numerical value achieved (between -3 and +2), ρ (rho) is the expected correlation of the goal scales, which is normally 0.3
[13,14].

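### The goal-achievement cut-off of GAS T-score above 50 contradicts the protocol's own scale: meeting all three goals exactly gives T = 50 and is classed as not achieved

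*Protocol article*

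**What the plan says.** All the relevant text is in the protocol article under Primary outcome measure.

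- Number of goals: "Three main problems of daily care and function will be determined by caregivers", and a goal is set for each.
- Weights: "A value of 1 is applied to" the weight of each goal.
- Scale, −3 to +2: "Baseline scores will be allocated as -2". Partial progress: "If a subject does not achieve the expected level but shows improvement, this is scored as -1". Goal met: "If the subject achieves the expected level, this is scored as 0". Goal exceeded: "If they achieve more than the expected outcome, this is scored as +1 for somewhat more and +2 for much more". A score of −3 marks deterioration.
- Aggregation: "A single aggregated score (T-score) can be produced by a standardized mathematical formula", with 50 as the constant term and ρ normally 0.3.
- Classification: "Subjects who achieve a GAS T-score >50 achieved their goals".

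The same section defines clinical relevance separately, as a gain of two or more points on one or more of the three goals. No other text says that a T-score of exactly 50 counts as achievement.

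**The concern.** The scale and the cut-off give different answers to the same question. On the scale, a goal is met at 0, and +1 or +2 is reserved for doing better than expected. The cut-off requires a T-score strictly above 50, which three goals scored 0 cannot reach. A subject who does exactly what was planned on every goal is therefore labelled as not having achieved the goals, while a subject who deteriorates on one goal can be labelled as having achieved them.

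At stake is the meaning of any goal-achievement proportion reported for the primary outcome measure. Families and clinicians will read such a proportion at face value.

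**Working it through.** **Inputs** (Primary outcome measure): three goals, each weight 1; scores from −3 to +2; ρ = 0.3; baseline −2 on each goal.

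**T-score.** T = 50 + 10·Σx / √((1 − ρ)·Σw² + ρ·(Σw)²).

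Denominator: √(0.7 × 3 + 0.3 × 9) = √4.8 = 2.191. One raw point is worth 10 / 2.191 = 4.56 T-score points.

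| Scores on the three goals | Sum | T | Rule T > 50 | Every goal at 0 or above? |
|---|---|---|---|---|
| −2, −2, −2 (baseline) | −6 | 22.61 | no | no |
| 0, 0, 0 | 0 | 50.00 | **no** | **yes** |
| 2, −1, −1 | 0 | 50.00 | no | no |
| 1, 0, 0 | 1 | 54.56 | yes | yes |
| 2, 2, −3 | 1 | 54.56 | **yes** | **no** |

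The value 50 for 0, 0, 0 holds for any ρ and any weights, because the numerator is zero. With the protocol's settings the next attainable value is 54.56, so the strict sign in effect demands a net result one point better than expected.

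**All profiles.** There are 6³ = 216 possible score combinations:

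- T > 50: 56 profiles. Of these, 30 contain at least one goal below 0, which leaves 56 − 30 = 26 with every goal met.
- T = 50 exactly: 25 profiles. One is 0, 0, 0; the other 24 contain a goal below 0.
- T ≥ 50: 56 + 25 = 81 profiles.
- Every goal at 0 or above: 27 profiles. The rule T > 50 accepts 26 of them; the one it rejects is 0, 0, 0.

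These are counts of possible patterns, not probabilities.

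**How the definitions compare in proportion (illustrative).** Assume three normally distributed goal scores, each with SD 1 and pairwise correlation 0.3, rounded and limited to −3 to +2. Before rounding, the sum has variance 3 + 6 × 0.3 = 4.8, so T has SD 4.56 × 2.191 = 10. That matches the SD of change for the baclofen group under Sample size calculation, since baseline is fixed. The planned baclofen mean is 22.6 + 12.5 = 35.1.

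| Mean T | T > 50 | T ≥ 50 | Every goal ≥ 0 |
|---|---|---|---|
| 35.1 (planned) | about 4.5% | about 10.7% | about 5.7% |
| 50 (expected level on average) | about 41% | about 59% | about 41% |

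Subject-level disagreement with the per-goal definition is about 3.2% for T > 50 and 5% for T ≥ 50 at the planned mean, and 12.9% and 18.2% at the expected-level mean.

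**Does it reach the design?** The section's stated sample size reproduces. The pooled SD is √((8.5² + 10²)/2) = 9.28, and a two-sided t-test at 5% for a difference of 12.5 has power 0.883 with 12 per group and 0.909 with 13. So 13 per group is right, and the cut-off plays no part in it.

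**The case against.** The strongest reply is that nothing in the stated analysis uses this cut-off. Univariate analysis compares T-scores between groups by t-test or Mann–Whitney test, Descriptive statistics tabulates means and SDs, and the sample size rests on mean change. A subject at 0, 0, 0 has gained two points on every goal and so already counts as clinically relevant improvement. All of this stands, and it limits the severity.

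A second reply is that the cut-off is taken from a cited source. That source is not available here, so whether it uses a strict sign cannot be checked. Either way, a citation does not reconcile the rule with the scale that this protocol defines.

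A reader might infer two stronger things. One is that the rule understates success or more than halves the number of achievers, from 10.7% against 4.5% at the planned mean. That holds only if T ≥ 50 is the true definition. The protocol's scale defines achievement per goal, and against every goal at 0 or above (5.7% and about 41%) the strict cut-off gives nearly the same proportions in both scenarios. The other inference is that changing the sign to ≥ is enough. It would admit 0, 0, 0 together with 24 profiles in which a goal was missed, and in the simulation it raises disagreement with the per-goal definition.

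**Conclusion.** The rule is wrong as written, and the matter is minor to moderate. That 0, 0, 0 is classed as not achieved is exact and needs no assumption. The step of 4.56 and the 25 boundary profiles out of 216 rest on three goals, unit weights and ρ = 0.3, as the protocol sets them. The proportions are illustrative and depend on the assumed distribution of goal scores.

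The fault is one of misclassification in both directions: the rule rejects the one profile that defines success on all goals, and it accepts 30 profiles in which some goal was not met. The documents do not support a claim of bias in the overall proportion, or of any effect on the primary test, the sample size or the clinical-relevance rule.

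**What to change.** Define achievement of the goals as a score of 0 or above on all three goals. This follows directly from the scale and covers 27 of the 216 profiles.

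If an aggregate cut-off is also wanted, state it as T ≥ 50 and label it as the net expected level reached, making clear that it does not show that every goal was met.

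The cost is a change of one or two sentences, best made before goal-achievement proportions are reported. The goal scores are already collected, and no assessment, sample size or primary analysis changes.

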### Secondary outcome measures

#### Dystonia

Videos of all patients will be made using the video protocol described by Monbaliu et al.
[20]. Blinded therapists or physicians will assess all videotapes and rate dystonia using the Barry-Albright dystonia (BAD) scale and the Dyskinesia Impairment Scale (DIS).

The BAD scale is a five point ordinal severity scale to assess secondary dystonia in eight body regions (eyes, mouth, neck, trunk, each upper and lower extremity)
[21]. Raters score dystonia as none, slight, mild, moderate or severe. A reduction of 25% or more, in comparison with the baseline score, is considered clinically significant. In our experience, interrater variability is high, but BAD scores are generally accepted as a measurement of dystonia and are widely used to assess dystonia.

Recently, a new instrument to measure dystonia in dyskinetic CP became available, the DIS
[20]. It consists of two subscales: dystonia and choreoathetosis. Scoring is carried out in 12 body regions all in two conditions (rest and activity). Both duration and amplitude are evaluated. Since this is a new instrument, we will use the DIS in addition to the BAD.

